### Outcome measures

Data collection is performed by three blinded, independent, calibrated outcome examiners at 0, 4, and 8 weeks after patient inclusion. For the primary objective (oral hygiene) and the main secondary objective (gingival inflammation) the outcome will be the value of indices collected during the third visit (8 weeks of follow up). Values range from 0 to 100%.

Two additional secondary objectives will be also considered: patient satisfaction after 8 weeks, and patient motivation for change after 4 and 8 weeks in each treatment arm. For the first secondary objective (patient satisfaction after 8 weeks), the Dental Visit Satisfaction Scale questionnaire [47] comprises 10 multiple choice questions (MCQ) scored on a 5-point Likert scale, and explores three aspects of patient satisfaction: information-communication, understanding-acceptance, and technical competence (Additional file 1). For the second secondary objective (patient motivation for change after 4 and 8 weeks), a questionnaire featuring 12 questions (MCQ or binary) derived from previous publications is used [46] (Additional file 2). Results from this questionnaire would allow a preliminary understanding of psychological factors predictive of patient motivation and readiness to change behavior.

### Data collection methods

To promote data quality, investigators and outcome examiners, who will assign scores, are trained in the plaque and gingival inflammation indices by means of group training sessions in real-life patients. To evaluate calibration on the primary outcome (plaque control), investigators and examiners are trained using a large number of pictures of teeth; inter-rater agreement is measured using the Kappa coefficient. Group training sessions and inter-rater agreement assessment are conducted before the beginning of patient inclusion.

For the primary and the main secondary outcome measures, data collection forms are generated through a public online platform [48]. For the patient-reported outcomes (remaining secondary objectives), patients enter their answers to the questionnaires directly on a dedicated and password-protected page of the e-CRF. No particular reward to promote participant retention and complete follow up has been instated.

### Data management

Investigators and outcome examiners enter the data into the e-CRF. Fields cannot be left blank. Interactive data controls will be applied for value ranges and presence of impossible values and for between-form coherence. A patient-operated e-CRF allows for the collection of patient-reported outcomes without the intervention of the study investigators. Data will be kept anonymous, with high-level security storage, and encryption of all data transfers, in compliance with French regulatory and European Clinical Research Infrastructure Network (ECRIN) requirements [49].

### Statistical methods

The statistical unit for analysis will be the patient. All of the patient’s teeth are considered for data collection but unerupted, impacted, or fractured teeth are excluded (site-related exclusion criteria). Six sites per tooth are examined.

The demographic and clinical characteristics of patients will be described for both the test and control groups with mean and standard deviation or median and interquartile ranges for quantitative variables, and number of subjects and percentages for qualitative variables. The analyses will be performed according to the intention-to-treat principle, modified to include only patients with available outcomes.

To respond to the primary objective, the mean plaque score in the test and control groups at 8 weeks will be calculated and compared using Student’s *t* test for unpaired data. The plaque score at the third visit will be modeled using a hierarchical model accounting for the correlation of the measures per patient and any possible inter-practitioner heterogeneity. The model will be adjusted on randomization stratification factors (center of inclusion, patient gender, and tobacco use) as well as the baseline value collected at the first visit. If necessary, other adjustment factors might also be considered. The main secondary objective (bleeding on probing) will be analyzed using Student’s *t* test (nonparametric test whenever relevant).

In cases of patient non-compliance with follow-up visits, sensitivity will be analyzed using the last outcome examiner’s assessment (last observation carried forward). Additionally sensitivity will be analyzed considering all missing data as equal to the test or control group’s mean values for the given visit. Candidate factors for subgroup analyses are patient age, patient gender, diabetic status, tobacco use, and at least one general medical condition.

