### Randomization

Patients are randomized using a computerized and centralized system via a specific website. Patients are one-stage randomized, stratified on the following potential confounders: investigation center (Lyon versus Liège), patient gender (male versus female), and patient current tobacco status (currently a tobacco user versus not currently a tobacco user). Because all patient characteristics must be entered in the e-CRF before interventions are assigned, sequence concealment is secured.

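### The primary objective is answered by a t test that ignores baseline plaque and the randomization strata, while the planned adjusted model has no stated role and an open covariate list

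*Protocol article*

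**What the plan says.** All the analysis text is in one paragraph of the article's Statistical methods section.

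- **Test tied to the primary objective.** An unpaired Student t test without covariates: "the mean plaque score in the test and control groups at 8 weeks will be calculated and compared using Student".
- **Model of the same outcome.** "The plaque score at the third visit will be modeled using a hierarchical model accounting for the correlation of the measures per patient" and differences between practitioners. It is adjusted for center, gender and tobacco use, "as well as the baseline value collected at the first visit".
- **Open clause.** "If necessary, other adjustment factors might also be considered". No criterion is given.
- **Unit of analysis.** "The statistical unit for analysis will be the patient".

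The Randomization section says that patients are "stratified on the following potential confounders", namely center, gender and current tobacco status. Outcome measures has plaque scored at 0, 4 and 8 weeks, so a baseline score is planned for every patient.

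The paragraph does not call the model primary, secondary or supportive, and does not say what happens if model and t test disagree. The only analyses presented as sensitivity analyses are the two ways of filling in missing visits.

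**The concern.** The trial stratifies on three factors because it regards them as potential confounders, and it measures the outcome before allocation. The test attached to the primary objective uses none of this. If baseline plaque predicts week-8 plaque, the t test leaves explainable variance in its error term and the confidence interval is wider than it needs to be. If the strata are prognostic, stratified allocation has already balanced them, so a standard error that ignores them is too large.

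The adjusted model that would recover this precision is already planned, but the reader cannot tell what it is for. Its covariate list can also grow after the data are seen. What is at stake is mainly power and precision, and secondarily which estimate the trial's conclusion will rest on.

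**Working it through.** **Inputs from the article (Sample size; Trial design).** 86 patients, 1:1 allocation, a difference of 10% in the PCR index (taken as 10 points), 80% power, two-sided alpha 5%, and 15% lost to follow up at 8 weeks.

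**Inputs not in the article.** The SD, the correlation ρ between baseline and week 8, and the share of variance R² explained by the strata. All three are assumed below.

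**1. The plan's own figure.** Without an SD, 86 cannot be reproduced from the article alone, so I solved for one. With SD 15 the normal formula gives 2 × (1.960 + 0.842)² × 15² / 10² = 35.3, so 36 per arm. Then 36 / 0.85 = 42.4, so 43 per arm and 86 in all. SD 15 is therefore consistent with 86 if the 15% loss is already included. If 86 were the evaluable number, the implied SD would be about 16.4 to 16.6.

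**2. The t test.** 86 × 0.85 = 73.1, so 73 analysed (37 and 36). The standard error is 15 × √(1/37 + 1/36) = 3.51. With 71 degrees of freedom the critical value is 1.994. The noncentrality is 10 / 3.51 = 2.85, which gives power of 80.2%. The half-width of the 95% CI is 1.994 × 3.51 = 7.0 points.

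**3. Baseline adjustment.** The residual SD is 15 × √(1 − ρ²), put through the same noncentral-t calculation. Spending four more degrees of freedom on covariates changes power by less than 0.1 percentage point.

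**4. Error rate if success could be claimed on either result.** Under the null hypothesis the two statistics are treated as bivariate normal with correlation √(1 − ρ²), each tested at 5%.

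| ρ (assumed) | 1 − ρ² | Residual SD | Power | 95% CI half-width | Either-result type I error |
|---|---|---|---|---|---|
| 0 (t test) | 1.00 | 15.0 | 80.2% | 7.0 | 5.0% |
| 0.1 | 0.99 | 14.9 | 80.6% | 7.0 | 5.5% |
| 0.2 | 0.96 | 14.7 | 81.8% | 6.9 | 5.9% |
| 0.3 | 0.91 | 14.3 | 83.8% | 6.7 | 6.4% |
| 0.5 | 0.75 | 13.0 | 90.0% | 6.1 | 7.3% |
| 0.7 | 0.51 | 10.7 | 97.6% | 5.0 | 8.3% |

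**5. Strata.** If the strata explain R² of the variance, the t test's actual two-sided level is about 2 × P(Z > critical value / √(1 − R²)). For R² = 0.10 this is 3.9% with the critical value 1.960 and 3.6% with 1.994. For R² = 0.20 it is 2.8% and 2.6%.

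**6. Steps 4 and 5 together.** The last column of the table assumes that the t test runs at a full 5%. If instead the strata explain 10 to 20% of variance, the either-result error falls to about 5.8–5.4% (ρ = 0.3), 6.6–6.0% (ρ = 0.5) and 7.4–6.6% (ρ = 0.7). The table's last column is therefore an upper value.

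**7. How often the two results would differ.** Under the planned effect, by the normal approximation with 36.5 per arm, the two analyses fall on opposite sides of 5% in about 7, 12 or 17% of trials at ρ = 0.3, 0.5 or 0.7.

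**The case against.** **The document does name a deciding test.** Only the t test is tied to the primary objective. The sentences on the model mention no between-group test. An unadjusted primary test followed by an adjusted model is a common pattern and the natural reading. A reader might infer that the plan has two primary p-values and so does not keep its 5% error rate. The text does not support that: nowhere does it permit success on whichever result is significant. What stands of the concern is that the model's role is unstated.

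**The t test is not wrong.** In a randomized trial it is valid, and ignoring the strata makes it conservative. A reader might infer that the trial is underpowered because of it. The figures do not show that: at SD 15 it has the stated 80%. This match holds by construction, since SD 15 was chosen to fit 86, but nothing in the article points to a shortfall caused by the test. The gain from adjustment is an improvement, not the repair of an error.

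**The correlation may be low.** Baseline plaque is scored after the motivational session, in which the patient demonstrates use of the brush and interdental tools. All patients receive new tools, and all are scaled and polished at visit 2. Each of these could weaken the link with week 8. This stands, and is why ρ = 0.1 and 0.2 are shown: there the gain is under 2 percentage points.

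**An article condenses.** A full covariate list is commonly left to the full protocol or the analysis plan. That is fair for detail. But the article itself assigns the unadjusted test to the primary objective and itself leaves the adjustment open, so the point concerns what it states.

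**Conclusion.** The point holds as an avoidable loss of precision with an unlabelled second analysis beside it. It is not an invalid test or a demonstrated loss of error control.

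- **Precision.** At SD 15 and 73 analysed, the t test gives up between about 0.4 percentage points of power (ρ = 0.1) and about 17 (ρ = 0.7). A gain of 10 points needs ρ near 0.5. The strata were not added to these power figures.
- **Model without a role.** This is the lesser risk. The either-result error of 5.5 to 8.3% is a ceiling over the same range of ρ. It applies only to a practice that the plan does not allow, and it is lower if the strata are prognostic. Additional covariates chosen later were not quantified.

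SD, ρ and R² are all assumptions. The direction does not depend on them beyond ρ or R² being above zero; the size does. Severity: should-fix.

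**What to change.** In Statistical methods:

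1. Name one primary analysis: the patient-level difference in week-8 PCR between arms, with estimate, 95% CI and p-value, from the already planned model with arm, baseline PCR, center, gender and tobacco use.
2. Keep the planned practitioner term in that model, or state that it is dropped. Say that the model has one week-8 score per patient, so that it agrees with the patient as unit of analysis.
3. Label the unadjusted t test as supportive.
4. Remove "If necessary, other adjustment factors might also be considered" from the primary model. Leave any further covariates to named sensitivity analyses.

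This costs wording only. Every covariate is already collected, and no patient, visit or measurement is added. The article's Trial status section has the trial still recruiting, so at that point the change could be made before the outcome data are analysed.

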The clinical examination for the secondary outcome is conducted immediately thereafter. A periodontal probe is used to assess the BOP index with six sites per tooth (disto-buccal, buccal, mesio-buccal, mesio-lingual, lingual, and disto-lingual). Criteria for the site to be coded “1” is bleeding within 30 s of probing [45], otherwise the site is coded “0”.

Then, the investigator records the personalized oral hygiene video. This video is recorded for all patients. The investigator uses a loupe-mounted miniature camera connected to a computer (Futudent Educam, Novocam Medical Innovations Oy, Helsinki, Finland). The video lasts approximately 3 min and displays the use of the electric toothbrush, the interdental brushes, and the dental floss. It contains audio instructions summarizing what was said to the patient during the consultation, and is to be watched while brushing the teeth.

After the video recording, the clinical part of the consultation is finished. Patients are then randomized by the center coordinator. Patients allocated to the control group are not given any further detail beyond their allocation. Patients allocated to the test group are registered in the text messages system and their personalized video is uploaded to the cloud portal by the investigator. The investigator instructs them on how the cloud portal and the text messages system work. Both the cloud portal and the text messages system are secured (see “Data management”, “Ethical considerations”, and “Discussion”). The cloud portable is accessible via any smartphone, tablet or computer with a web browser, irrespective of their operating system, and there is no need to install an application in an attempt to maximize technical compatibility. As no application is installed, no notifications will be used to remind the patient about watching the video: only text messages will be used.

The difference between control and test groups is the availability of the personalized oral hygiene video through the cloud server and the registration of the patient in the interactive text messages system. The two follow-up appointments are scheduled, and the visit is brought to an end. Patients in either of the two groups are not contacted by investigators between visits, except for administrative reasons such as rescheduling an appointment.

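### The main secondary outcome (bleeding on probing at 8 weeks) is planned without baseline or stratum adjustment, which gives up precision that the collected data would supply

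*Protocol article*

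**What the plan says.** The Statistical methods section gives BOP a single sentence: "The main secondary objective (bleeding on probing) will be analyzed using Student", completed by the name of the t test and a bracketed alternative, "nonparametric test whenever relevant". It names neither the alternative test nor the condition for using it.

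Plaque is treated more fully in the same paragraph. After a t test for the primary objective, the text adds: "The plaque score at the third visit will be modeled using a hierarchical model". It then specifies the covariates: "The model will be adjusted on randomization stratification factors (center of inclusion, patient gender, and tobacco use) as well as the baseline value". That model is tied to the plaque score; nothing extends it to BOP.

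The covariates exist for BOP as well. Under Intervention, visit 1: "A periodontal probe is used to assess the BOP index with six sites per tooth". Outcome measures confirms the timing: "Data collection is performed by three blinded, independent, calibrated outcome examiners at 0, 4, and 8 weeks after patient inclusion". The visit 1 text places allocation after these measurements: "After the video recording, the clinical part of the consultation is finished. Patients are then randomized by the center coordinator". The Randomization section requires patient characteristics to be entered before assignment.

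**The concern.** The two examiner-assessed outcomes are collected at the same visits, on the same sites and by the same examiners, yet only plaque is modelled with its baseline value and the stratification factors. No reason is given for the difference. Baseline BOP is taken after the motivational interview but before allocation, so it is a legitimate covariate. The three stratification factors shaped the allocation and then play no part in the BOP comparison.

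The sample size was set on plaque alone, so the power for BOP is whatever results. An estimate with avoidable noise is more likely to leave the main secondary question unanswered. The nonparametric option adds a smaller difficulty: with no trigger stated, the reader cannot tell which test will be the main one. The usual choice, a rank test, would not estimate the difference in means that the t test targets.

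**Working it through.** **Inputs from the article.** Sample size section: 86 patients, 10-point plaque difference, 80% power, two-sided 5% alpha, 15% expected loss. Trial design and Randomization: 1:1 allocation, strata 2 × 2 × 2 = 8. No BOP standard deviation, BOP target difference or baseline-to-week-8 correlation is given.

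**The plan's own figure.** The 86 cannot be reproduced, because no SD is stated even for plaque. Back-solving with SD = 10 / [(1.96 + 0.842) × √(2/n)]:
- if 86 already allows for the loss, n = 86 × 0.85 / 2 = 36.55 per arm and SD ≈ 15.3 (15.05 with the t distribution);
- if 86 is the evaluable number, n = 43 per arm and SD ≈ 16.5 (16.4 with the t distribution).

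Both are possible readings. The relative gains below are the same under either.

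**Gain from baseline adjustment.** With ρ the correlation between baseline and week-8 BOP, the variance of the arm difference falls from 2σ²/n to about 2σ²(1 − ρ²)/n. The interval width is multiplied by √(1 − ρ²), and the standardized difference is divided by it. Power is shown for a comparison that has 80% without adjustment. The last column is 86 / (1 − ρ²).

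| Assumed ρ | Variance ratio | CI width ratio | Power | Unadjusted N equal to 86 adjusted |
|---|---|---|---|---|
| 0.2 | 0.96 | 0.98 | 82% | 90 |
| 0.3 | 0.91 | 0.95 | 84% | 95 |
| 0.4 | 0.84 | 0.92 | 86% | 102 |
| 0.5 | 0.75 | 0.87 | 90% | 115 |
| 0.6 | 0.64 | 0.80 | 94% | 134 |
| 0.7 | 0.51 | 0.71 | 97.5% | 169 |

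Hand check at ρ = 0.5: (1.96 + 0.842) / 0.866 = 3.235; 3.235 − 1.96 = 1.275; the normal probability is 0.90. The formula ignores the small cost of estimating the covariate effects, so the gain at the bottom of the range is slight.

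**Ignoring the strata.** Simulation under no effect: 10,000 runs, 72 patients in 8 equal strata, allocation balanced within strata, unadjusted t test at a nominal 5%.

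| Share of BOP variance explained by strata (assumed) | True type I error |
|---|---|
| 0% | 5.0% |
| 10% | 4.0% |
| 20% | 3.3% |
| 30% | 2.1% |
| 40% | 1.4% |

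The error is on the safe side, but a test that runs below its nominal level also wastes power.

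**The open choice of test.** Simulation with 37 per arm, under a normal and under a skewed distribution: taking the smaller of the t-test and rank-test p values gives a type I error of about 5.9% in both. This is an upper bound for choosing freely between those two tests, not something the plan proposes.

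**The case against.** The case for leaving the plan alone has several sound parts. A randomized comparison by t test is unbiased, and its standard error already allows for chance baseline imbalance. Stratification limits imbalance on center, gender and tobacco use by design. BOP receives the same test as the first analysis of plaque. The article is a condensed document, and an analysis plan not shown may add a model.

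A reader might infer more than the text supports, in four ways:
- **That the t test is biased or invalid.** It is neither. If the strata matter, it is conservative.
- **That adjustment is worth a third more patients, or nearly double.** Those figures need ρ = 0.5 (1/0.75 = 1.33) and ρ = 0.7 (1/0.51 = 1.96), and no correlation is documented. Both arms receive motivational interviewing, an electric toothbrush and full-mouth scaling at week 4, all of which could weaken the link with baseline.
- **That the choice of test will be made after seeing results by arm.** The text gives no timing, and the Trial design section says data analysts are blinded to allocation. Blinding does not replace a stated trigger, but the charge is not established.
- **That tobacco use and center are known to affect bleeding here.** The Background links smoking to periodontitis, and the Randomization section calls the factors only possible confounders. The examiners are calibrated.

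These points reduce the size of the concern without removing it. The article does name the BOP analysis, and that analysis leaves out covariates already in hand.

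**Conclusion.** The point stands as a matter of efficiency for the main secondary outcome, not of validity. For assumed ρ of 0.2 to 0.7, baseline adjustment would reduce the variance by 4% to 49%, with the lower part of the range plausible. Adding the strata would remove the conservatism of the unadjusted test to whatever extent they predict BOP, which is unknown. The undefined nonparametric option is a lesser defect. Reading the BOP analysis as unadjusted rests on the absence of any covariate in its sentence, beside the explicit adjustment for plaque.

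**What to change.** State one main analysis for BOP: a patient-level model of week-8 BOP with arm, baseline BOP, center, gender and tobacco use, and with the practitioner term if that is kept for plaque. Report the adjusted mean difference with its 95% confidence interval. If the distribution is skewed, use robust or bootstrap standard errors, so that the same difference is still estimated. Keep the t test or a named nonparametric test as a sensitivity analysis.

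The cost is a change of wording. It needs no new data or visits, and it changes no sample-size figure, since 86 was set on plaque.

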### Sample size

A literature review found that behavioral interventions, similar to the patient education strategy explored in this trial, allow up to 15% reduction of dental plaque [21, 36–39]. However, to the best of our knowledge, there is no publication examining the eHealth concept for patient motivation for oral hygiene proposed herein. A conservative estimate of 10% reduction in PCR index was therefore chosen for the test group compared to the control group.

A total of 86 patients enables us to show a 10% difference in the PCR index between the two groups with 80% power, using a bilateral test with an alpha risk of 5%. At 8 weeks, 15% of patients are expected to be lost to follow up (calculated by nQuery Advisor 7.0) [40].

To encourage recruitment, the investigators organize regular communications with colleagues of the teaching hospitals, involve student representatives in the process by having them promote the study among their classes, and regularly have the study leaflet as the desktop image of computers in the relevant hospital departments. In addition, students who refer a patient for inclusion in the protocol receive extra points for their periodontology practical examination and the patient is referred back to them for the next phases of periodontal therapy.

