A brief clinical examination is conducted, and the outcome examiner then collects the clinical data. Data collection is conducted following the same protocol as for the first visit. Results are delivered to both the investigator and the patient, and are stored in both the e-CRF and the patient’s electronic healthcare records.

The investigator then conducts full-mouth supra-gingival and juxta-gingival tooth scaling and polishing (Acteon ultrasonic tip number 1 and Newtron LED handpiece, Satelec Acteon, Merignac, France). The investigator ensures thorough removal of calculus but avoids instrumenting the gingival pockets. Following completion of the scaling, patients are invited to rinse with a solution containing 0.12% chlorhexidine digluconate (Paroex, Sunstar France, Levallois Perret, France). Additional supplies of interdental brushes and floss are given to the patient if required. The next appointment is confirmed and the second visit is brought to an end.

#### Visit 3

At the third visit (T0 + 8 weeks), patients are first asked to complete the same questionnaire about their motivation for and behaviors in oral health they completed at the second visit. Then, a short (< 5 min) recall about oral hygiene methods is proposed to the patient and conducted by the investigator if needed.

A brief clinical examination is conducted, and the outcome examiner then collects the clinical data following the same protocol as for the first visit. Results are delivered to both the investigator and the patient, and are stored in both the e-CRF and the patient’s electronic health records.

At the end of the appointment, the patient is asked to complete a satisfaction questionnaire specially designed for dental care (Dental Visit Satisfaction Scale [47]). Again, data are directly entered by the patient into the e-CRF and investigators are blinded to the answers.

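### Filling missing week-8 plaque scores with the patient's own group mean cannot test robustness: in the t test it repeats the complete-case difference with a standard error about 15% too small

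*Protocol article*

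**What the plan says.** Under Statistical methods, the protocol article defines the main analysis as a modified intention-to-treat analysis limited to patients whose outcome is available. The week-8 plaque control record (PCR) scores are compared by an unpaired Student t test. A hierarchical model adjusted for baseline and the stratification factors is also planned.

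Two sensitivity analyses for missed visits follow. The first uses the outcome examiner's last "assessment (last observation carried forward"). In the second, "sensitivity will be analyzed considering all missing data as equal to the test or control group"'s mean at the visit concerned. No other method for missing scores is named.

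Under Sample size, "15% of patients are expected to be lost to follow up" at 8 weeks, and "A total of 86 patients enables us to show a 10% difference in the PCR index between the two groups" at 80% power and a two-sided 5% level.

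**The concern.** A sensitivity analysis for missing data should show whether the conclusion would change under a different, credible assumption about the patients who were not seen. Filling each gap with the mean of the patient's own arm does not do this. The filled values add nothing to the difference between arms and nothing to the within-arm sum of squares, yet they raise the patient count and the degrees of freedom. The check can only agree with the complete-case t test, and it always looks more certain.

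The other check has a different weakness. It puts an earlier score in place of the week-8 score. The visit 1 score is taken before any home use of the new routine. The visit 2 score is taken before the scaling done at that visit: under Visit 2, data collection comes first and then "The investigator then conducts full-mouth supra-gingival and juxta-gingival tooth scaling and polishing". If plaque falls during the trial, carried scores are too high, and the arm with more dropout looks worse.

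With a complete-case main analysis and a sizeable expected loss, these two checks are the only protection against attrition bias that the article states.

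**Working it through.** **Inputs from the article.** 86 patients, 1:1, so 43 per arm; two-sided 5%; 15% loss, so 0.15 × 86 = 12.9, about 13 missing and 73 observed; unpaired t test at week 8. No SD is given, but it cancels from the mean-filling result.

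**The plan's own figure.** Without an SD, 86 cannot be reproduced. It fits an assumed SD near 15 with loss included (36 per arm; 36/0.85 = 42.4, so 43 per arm), or an SD near 16.4 with no allowance for loss. The result below holds either way.

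**Own-arm mean filling, point estimate.** Adding values equal to an arm's mean leaves that mean unchanged. The filled difference therefore equals the complete-case difference exactly in the unadjusted t test, and only approximately in the adjusted hierarchical model.

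**Own-arm mean filling, standard error.** Let n be the number observed (n1 + n2) and N the number after filling (N1 + N2). The sum of squares is unchanged but is divided by N − 2 instead of n − 2, so

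SE ratio = √[(n − 2)/(N − 2)] × √[(1/N1 + 1/N2)/(1/n1 + 1/n2)]

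With 37 observed of 43 per arm: √(72/84) × √(37/43) = 0.926 × 0.928 = 0.859.

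**Type I error of the check** = 2 × P(t with n − 2 df > critical t with N − 2 df × SE ratio).

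| Observed, of 43 + 43 | Missing | SE ratio | Type I error |
|---|---|---|---|
| 41 + 41 | 4.7% | 0.953 | 6.2% |
| 39 + 39 | 9.3% | 0.906 | 7.6% |
| 37 + 37 | 14.0% | 0.859 | 9.2% |
| 36 + 37 | 15.1% | 0.847 | 9.65% |
| 36 + 36 | 16.3% | 0.835 | 10.1% |
| 34 + 34 | 20.9% | 0.788 | 12.2% |

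Because the estimate only shifts with the true difference, 95% interval coverage is 100% minus these figures, about 90-91% near the planned loss. If 86 is the number analysed and 101 or 102 are enrolled, the ratio is 0.850 or 0.842 and the error 9.5% or 9.9%. Simulation with 15% missing at random in each arm gave 9.9% for own-arm filling and 5.1% for the complete-case test.

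**Other readings of the sentence.** With 6 of 43 missing per arm (14%):

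- Control mean for everyone: the test mean becomes 0.86 × test + 0.14 × control, so the difference shrinks by 14%. Simulated type I error at 15% loss in each arm is 5.1%. It rises to 6.4% when dropout is 10% in one arm and 20% in the other, and to 8.4% at 5% and 25%.
- Opposite arm's mean: the difference is multiplied by 1 − 2 × 0.14 = 0.72. Simulated type I error at 15% loss is about 1.7%.

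**Last observation carried forward (illustration only).** The article gives no plaque course and no dropout by arm, so every input here is assumed, and dropout is taken as unrelated to score.

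- Visit 1 carried, no true effect: bias = dropout gap × fall in PCR. With 20% against 10% dropout, falls of 10, 20 and 30 points give 1, 2 and 3 points against the arm with more dropout.
- Visit 1 carried, equal 15% dropout, true difference −10: −10 × 0.85 = −8.5.
- Visit 2 carried, control/test means 38/30 at week 4 and 30/20 at week 8 (true difference −10). With dropout of 20% control and 10% test: (20 + 0.1 × 10) − (30 + 0.2 × 8) = 21.0 − 31.6 = −10.6. With 15% in both: (20 + 0.15 × 10) − (30 + 0.15 × 8) = 21.5 − 31.2 = −9.7.

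**The case against.** The strongest reply is that these are sensitivity analyses. A reader might infer from the 9-10% that the trial's false-positive rate is inflated. It is not: the primary t test uses observed patients only and keeps its 5% level. Nothing in the article says that a check's p-value decides the conclusion.

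Second, the sentence does not say outright whose mean is used. Own-arm filling is the natural reading, but under the other readings the estimate moves and the inflation is smaller, absent or reversed. This stands as a condition on the result and as a reason to rewrite the sentence.

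Third, it is tempting to say that last observation carried forward is invalid, or that it exaggerates the benefit by a known amount. The article supports neither. It gives one overall loss figure and no plaque trajectory, so any size is assumed. With equal dropout the check is mildly conservative in the examples above. If dropout depends on the score, the complete-case estimate can itself be biased, and a check that disagrees with it is doing its job. The Abstract names relapse as a central problem, so a return towards an earlier score is a coherent stress scenario. The point about scaling does not apply to patients lost before visit 2.

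What remains is that unequal dropout is plausible by design. Only test-arm patients receive the text messages, which recall the next appointment and go out the day before visits 2 and 3. Control patients are contacted between visits only for administrative reasons.

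Last, variance handling after imputation might be left to an analysis plan that is not shown. The filling rule itself is stated, however, and a variance correction would not help: the estimate would still be the complete-case one.

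**Conclusion.** The concern holds for group-mean filling on the own-arm reading. In the unadjusted t test the check returns the complete-case difference, shrinks the standard error to about 0.84-0.86 of its correct value and has a type I error of about 9-10% at the expected 15% loss. These figures need no assumed SD; they rest on 43 per arm and the stated loss, and change little if 86 is the number analysed. Exact equality of the estimates is limited to the unadjusted test.

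For last observation carried forward only a qualitative statement is supported: if plaque falls during the trial and dropout differs between arms, the difference is biased against the arm that loses more patients.

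The consequence is a robustness check that gives no information and too much precision, not a faulty primary analysis.

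**What to change.** Replace group-mean filling with one of two methods:

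- multiple imputation carried out by arm, using baseline PCR, week-4 PCR and the stratification factors, with results pooled by Rubin's rules; or
- a likelihood-based mixed model on the scores from all visits, which needs no pooling.

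Both can use the scores already collected at 0, 4 and 8 weeks. Add a delta or tipping-point analysis over a prespecified range, to probe scores that are missing not at random. The article gives no basis for particular delta values, so the range should be justified when it is set. Drop last observation carried forward, or keep it only as a labelled secondary scenario. If any mean filling is kept, state which group's mean is used.

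The cost is revised wording, a little more analysis work and somewhat wider intervals than mean filling would give. No new data or patients are needed, and the article reports the trial as still recruiting.
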